## Abstract

**Introduction:**

The rising prevalence of stroke and stroke-related disability witnessed globally over the past decades may cause an overwhelming demand for rehabilitation services. This situation is of concern for low-income and middle-income countries like India where the resources for rehabilitation are often limited. Recently, a smartphone-enabled carer-supported educational intervention for management of physical disabilities following stroke was developed in India. It was found to be feasible and acceptable, but evidence of effectiveness is lacking. Hence, as a step forward, this study intends to evaluate clinical effectiveness of the intervention through a randomised controlled trial.

**Methods:**

The objective of the study is to evaluate whether the ‘Care for Stroke’ intervention is clinically and cost-effective for the reduction of dependency in activities of daily living among stroke survivors in an Indian setting. This study is designed as a randomised controlled trial comparing people who received the intervention to those receiving standard care. The trial will be pragmatic and outcome assessor-blinded. The primary outcome for the study is dependency in daily living measured by the Modified Rankin Scale (MRS). A total of 266 adult stroke survivors who fulfil the eligibility criteria will be randomised to receive either ‘Care for Stroke’ intervention or standard treatment and will be followed up for 6 weeks. The main analyses will compare participants allocated to the ‘Care for Stroke’ intervention versus those allocated to the standard treatment group on an ‘intention-to-treat’ basis, irrespective of whether the participants received the treatment allocated or not. The dichotomised MRS scores (0–3 and 4–6) in both the groups will be used to calculate the effect estimates with a measure of precision (95% CI) and presented in the results of the trial.

**Ethics and dissemination:**

The Indian Institute of Public Health-Hyderabad/Public Health Foundation of India – Independent Institutional Ethics Committee and the Ethics Committee of the London School of HygieneandTropical Medicine. Dissemination will be through peer-reviewed publications.

**Trial registration number:**

Clinical Trial Registry of India CTRI/2017/07/009014.

Strengths and limitations of the studyEffectiveness of the intervention will be established through a randomised controlled trial.The trial protocol was pilot tested and was found feasible.This is the first ever stroke trial in India evaluating a mHealth rehabilitation intervention.Stringent inclusion criteria for participant recruitment.The duration of follow-up in the trial is not long.

## Introduction

Globally around 15 million people suffer from stroke each year and a quarter of them experience permanent disability.^1^ Much of this burden is borne by low-income and middle-income countries (LMICs).^2^ The increase in prevalence of stroke^3^ and consequently of stroke-related disability may cause an overwhelming demand for rehabilitation services worldwide.^3^ This situation is especially of concern for LMICs like India where the resources for rehabilitation are often limited.^3^

Stroke is one of the leading causes of death and disability in India. Given the paucity of data on stroke in India, a systematic review of population-based studies on stroke in India was conducted. Studies included in this review showed that the crude stroke prevalence during the past two decades in India ranged from 44/100 000 persons to 559/100 000 persons,^4^ and the cumulative incidence of stroke in India ranged from 105–152/100 000 person per year.^4^ These estimates on stroke incidence and prevalence are found to be higher than those reported from high-income countries.^5^ The growing burden of stroke-related disability and the unmet need for rehabilitation following stroke in India poses a major public health challenge.

There is a paucity of global evidence on the effectiveness of therapy-based stroke rehabilitation, especially in long-term care.^6 7^ Available evidence shows that there is no single physical rehabilitation approach that is more effective than combinations of care.^8^ Provision of information to stroke survivors and caregivers has been shown to improve functional outcomes.^9^ However, the best way to do this is still unclear. Recently, mHealth options are rising substantially and mobile technology has been substantially used to communicate for health-related reasons. Though mHealth strategies have developed various solutions to meet the needs of stroke survivors, the best way to use this approach in stroke rehabilitation is also still unclear.^10^ There is insufficient evidence for tele-rehabilitation services.^11^ This context provides a strong grounding for the development of cost-effective multidimensional stroke rehabilitation interventions to meet the demands of the stroke survivors. In the absence of organised stroke care services and with the limited resources available for rehabilitation, a comprehensive approach to address the growing burden of stroke-related disability in India becomes pertinent.^12^ This approach could be pivotal in integrating various strategies for rehabilitation^3^ (educational, community-based rehabilitation, digital technology, self/supported management and so on). It could also be useful for targeting the full range of impacts of stroke, including on impairments, activity limitations and participation restriction, as outlined in the ‘biopsychosocial conceptualisation of disability framework’ for the intervention, as proposed by the International Classification of Functioning Disability and Health (ICF).^13^

A smartphone-enabled carer-supported educational intervention was developed by our group for the management of physical disabilities following stroke in India.^14^ This intervention was named as ‘Care for Stroke’. It was developed using the systematic approach to development and evaluation of complex interventions, as recommended by the Medical Research Council (MRC) in the UK.^15 16^ We intended to bridge the gaps in access to stroke services through this innovative intervention which optimises relevant public health practice with the support from mobile devices such as smartphones, personal digital assistants and other wireless devices.^17^ To the best of our knowledge, there is no other stroke rehabilitation intervention enabled through mHealth platforms that are available and relevant to India.

The intervention was evaluated for its feasibility and acceptability in an Indian context.^18^ The intervention includes information about stroke and the ways to manage physical disability following stroke. It contains a practical demonstration of functional poststroke exercises to acquire the functional abilities necessary to perform everyday tasks, adaptive techniques to perform one’s own daily activities independently and a specific section on assistive devices that could enable participation of the stroke survivors in their daily tasks.^14^ Findings from the pilot-testing showed that the ‘Care for Stroke’ intervention was feasible and acceptable in the Indian context.^18^ About 95% of the stroke survivors and all the caregivers (100%) rated the intervention as ‘excellent’, based on its (a) overall credibility, (b) feasibility and (c) user-friendliness.^18^

However, feasibility and acceptability alone will not be sufficient to inform implementation and scalability.^16^ Nor will it be enough in order to advocate for change in policy towards implementation of an intervention.^19^ Investigating the intervention clinical and cost-effectiveness will provide insights for planning, implementation and the potential scalability of the intervention, especially in countries with limited resources. Given the methodological quality of the available evidence,^9–11^ there is a pressing need to conduct a rigorous (randomised, controlled, sufficiently powered) clinical trial to demonstrate the effectiveness of the ‘Care for Stroke’ intervention.

## Objective

The objective of the randomised controlled trial is to evaluate whether the ‘Care for Stroke’ intervention is effective for the reduction of dependency in activities of daily living among stroke survivors compared with people receiving standard treatment in an India setting. The primary outcome for the study is disability measured by the modified Rankin Scale (MRS).

## Methods

### Overview

This trial will be a pragmatic, randomised, outcome assessor-blinded trial to quantify the effectiveness of the Care for Stroke intervention on reducing dependency in activities of daily living following stroke. A total of 266 adult stroke survivors who fulfil the eligibility criteria will be randomised to receive either ‘Care for Stroke’ intervention or standard treatment and will be followed for 6 weeks. The flow chart of the entire trial process is provided in figure 1.

**Figure 1 F1:**
[figure not shown]
Flow chart of the Care for Stroke trial.

### Pragmatic design and the uncertainty principle

The effectiveness of the intervention in routine practice can be assessed using the pragmatic trial design. Until now, there is no evidence for effectiveness of stroke rehabilitation interventions that is unidisciplinary, led by a physician, neurologist or a physiotherapist alone.^12^ However, a physiotherapist or physician-driven unidisciplinary rehabilitation is what is commonly practised in the context of stroke rehabilitation in India.^12^ Given the lack of evidence, there is a natural uncertainty among the health professionals involved in provision of stroke care about what intervention could work best for the stroke survivors in an Indian context. The eligibility for participant recruitment in the ‘Care for Stroke Intervention’ trial will be based on this uncertainty principle. This approach to assess participant eligibility is well established.^20^

## Setting

### Participant recruitment

Participants will be identified using their contact details from treatment records for their first ever stroke. These details for stroke survivors in India exist in two places. Participant diagnosis and details can be collected from the hospital records from which an individual received treatment for his/her stroke. It is also available at the government health insurance department where the cost of the treatment for stroke is covered by this insurance department. Hence, participants will be identified through both these options. The identified participants will be contacted at their home for consent and recruitment. The intervention will be provided to the participants at home and they will be asked to use the intervention in their home.

## Eligible participants

### Inclusion criteria

Adults (aged ≥18 years).Recent diagnosis of first ever stroke as defined by the WHO.^21^Any level of stroke severity (score 1–42, according to National Institute of Health (NIH) stroke scale.^22 23^)Stroke survivor medically stable (reaching a point in medical treatment where life-threatening problems following stroke have been brought under control).Poststroke functional status of the stroke survivor: requiring assistance of at least one person to perform daily activities such as transfers, self-care and mobility (ie, scoring less than the maximum score obtainable in one or more components of the Barthel Index^24^).Stroke survivor residing with a primary caregiver (family member) at home.

## Exclusion criteria

Severe cognitive difficulties (scoring >1 in orientation, executive function, inattention and language components of the NIH Stroke Scale for cognition^25^).Severe communication problem (scoring >1 in dysarthria and best language component of the NIH Stroke Scale^22 23^).Stroke survivor functionally dependent because of other pre-existing conditions (eg, amputation, fracture and dementia).Stroke survivor without a primary caregiver.Stroke survivor unwilling/unable to adhere to the study protocol.Stroke survivors who did not meet the training requirements regarding operation of a smartphone. This criterion was deliberately placed just to make sure that there is no dropout after the recruitment. It was based on the observations from previous piloting.

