## Randomisation

Stroke survivors will receive all-usual treatment for stroke. Participants eligible for inclusion will be identified by a trial investigator. The eligible participants will be initially contacted by telephone and they will be visited in person at their home by the investigator to share the details about the study to the participant and the identified caregiver. A participant information sheet outlining the study objectives, risks and benefits along with brief information sheet about stroke will be provided to the participant. Written informed consent for participation in the intervention will be sought from all participants or from the next of kin if the participant is unable to consent.

An entry form will be used to collect baseline information including the contact details of the participant and the identified caregiver. This information will be forwarded to the independent randomisation centre and the participants eligible for inclusion will be randomised to the intervention or control arm in a 1:1 ratio using a secure, central, password-protected, web-based system. The intervention will be started within 24 hours of randomisation.

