## Intervention arm

The stroke survivor and their caregiver will receive 45–60 min of training on accessing and use of the intervention (watching videos) via the smartphone. Participants will then be provided with a smartphone preloaded with the ‘Care for Stroke’ intervention and asked to try it out on their own. Three or more errorless attempts to retrieve any required part of the intervention from the smartphone will be considered successful training. After successful training, participants will be provided with a smartphone loaded with the intervention and will be asked to use this intervention at their discretion at home over a 6-week period.

The identified caregivers of stroke survivors will be asked to support the stroke survivors as and when necessary to access the intervention from the smartphone. The participants will be telephonically supported at least once in a week during the intervention period. The telephonic support is essentially to remind and obtain updates from the participants or identified caregivers on utilisation of the intervention. A summary of this conversation will be documented and the notes will be kept privately in a locked cupboard. The participants in the intervention arm will not be restricted from receiving standard treatment for their stroke.

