## Control arm

Participants in the control arm will receive standard poststroke rehabilitation services. In general, the standard treatment may include provision of physiotherapy (45 to 60 min) at home or in a clinic facility for the stroke survivors based on goals set by the specific therapist or a rehabilitation team.

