## Analysis

The main analyses will compare all those allocated to the ‘Care for Stroke’ intervention with those allocated to the standard treatment group on an ‘intention-to-treat’ basis, irrespective of whether the participants received the treatment allocated or not. The imbalance in recruiting equal number of participants if any will be addressed during the analysis phase using appropriate statistical techniques. The dichotomised MRS scores (0–3 and 4–6) in both the groups will be used to calculate the effect estimates with a measure of precision (95% CI) and presented in the results of the trial. Subgroup analysis for the primary outcome will be based on stroke severity, location of the participant (urban/rural), gender and age at stroke. Interaction tests will also be used to test whether the effect of treatment (if any) differs across these subgroups.

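### Failing smartphone training is an exclusion criterion, but the only training and pass rule described belong to the intervention arm after randomisation, so as written the criterion can be applied in one arm only or not at all

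*Protocol article*

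**What the plan says.** Five sections of the protocol article bear on this.

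- **Exclusion criteria.** One item is "Stroke survivors who did not meet the training requirements regarding operation of a smartphone". The reason follows: "This criterion was deliberately placed just to make sure that there is no dropout after the recruitment", with reference to the earlier pilot.
- **Randomisation.** The sequence is identification, telephone contact, home visit, information sheet, consent, entry form with baseline data, then 1:1 allocation of those found eligible. No smartphone training or test is mentioned. "The intervention will be started within 24 hours of randomisation".
- **Intervention arm.** Survivor and caregiver "will receive 45–60 min of training on accessing and use of the intervention (watching videos) via the smartphone". The pass rule is "Three or more errorless attempts to retrieve any required part of the intervention from the smartphone will be considered successful training". Then: "After successful training, participants will be provided with a smartphone loaded with the intervention". Nothing is said about a person who does not pass.
- **Control arm.** "Participants in the control arm will receive standard poststroke rehabilitation services". No training is described.
- **Analysis.** Everyone allocated is compared by intention to treat, "irrespective of whether the participants received the treatment allocated or not".

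**The concern.** An exclusion criterion has to be assessable in the same way in everyone, before allocation. This one turns on the result of a training session, and the only such session in the article is part of the intervention that one arm receives. A control participant has no training result, so no control can meet the criterion.

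Taken literally, the criterion would remove people from the intervention arm alone, after randomisation. If those who cannot retrieve the videos without error tend to be more impaired, that arm's proportion with MRS 4–6 would fall without any treatment effect. The comparison would favour the intervention, whether it is read as superiority or under the non-inferiority wording in Sample size estimation. An allocated participant who is withdrawn without a 6-week MRS cannot be recovered at the analysis stage.

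**Working it through.** **Step 1: can the provisions all be carried out as written?**

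- *The criterion is applied through the training under Intervention arm.* Only people already allocated to that arm can fail. Excluding them is one-sided and contradicts the Analysis section, which keeps everyone allocated.
- *The Analysis section prevails.* People who fail stay in the intervention arm, and the exclusion item has no effect.
- *The same training and pass rule are moved before randomisation for everyone.* The criterion could then work, but future controls would have 45–60 minutes of training on the intervention's own content, and the section that places training in the intervention arm would be wrong.

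Each route leaves at least one section needing correction.

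**Step 2: how large could the bias be if failers were dropped from one arm?**

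Inputs from Sample size estimation: 133 per group, 50% dead or dependent, 20% difference, one-sided 5% level, 90% power, 20% loss. As a check, a non-inferiority calculation with 50% in both arms and a 20-point margin gives (1.645 + 1.282)² × (0.25 + 0.25) / 0.20² = 107.05 per arm, and 107.05 / 0.8 = 133.8. Truncated, this is the stated 133 per arm (266); rounding up at each step gives 108 / 0.8 = 135 per arm, or 270. So 50% is a reasonable base rate. That it applies to MRS 4–6 in this population is an assumption.

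Assumed, because the article gives neither: the proportion *f* who fail training, and the proportion *q* of failers who would be MRS 4–6. Assume also no true effect.

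- Intervention-arm rate after exclusion = (0.5 − *f q*) / (1 − *f*)
- Spurious benefit = 0.5 − that rate = *f* (*q* − 0.5) / (1 − *f*)

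Example: *f* = 0.10, *q* = 0.8 gives (0.5 − 0.08) / 0.9 = 46.7%, a spurious benefit of 3.3 points.

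Spurious benefit in percentage points:

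| Fail training | q = 60% | q = 70% | q = 80% | q = 90% |
|---|---|---|---|---|
| 5% | 0.5 | 1.1 | 1.6 | 2.1 |
| 10% | 1.1 | 2.2 | 3.3 | 4.4 |
| 15% | 1.8 | 3.5 | 5.3 | 7.1 |
| 20% | 2.5 | 5.0 | 7.5 | 10.0 |

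Two yardsticks from the article: the planned difference is 20 points, so the worst corner is half of it and most cells are far below. The cited meta-analysis has a 21% odds reduction from 50%, which is 0.79 / 1.79 = 44.1%, a benefit of 5.9 points. Several cells approach or exceed that.

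**Step 3: effect on a one-sided 5% superiority test, with 20% loss in each arm.**

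For *f* = 0.10 and *q* = 0.8: 120 v 133 participants, or 96 v 106.4 after loss. The pooled rate is (96 × 0.4667 + 106.4 × 0.5) / 202.4 = 0.484. The pooled standard error is 0.0704 and the unpooled one 0.0703. The chance of a false positive is P(Z > (1.645 × 0.0704 − 0.0333) / 0.0703) = P(Z > 1.17), about 12%. Over the whole table it runs from about 6% to about 39%.

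**The case against.** A reader might infer that the trial withdraws training failers from the intervention arm after allocation and that intention to treat is therefore broken. The article does not support that. It nowhere says that anyone who fails is withdrawn, excluded or replaced. The item stands among eligibility criteria, and Randomisation allocates people found eligible, after a home visit at which a check could be made. The stated aim of avoiding dropout after recruitment also fits a check made before it.

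Silence in Randomisation proves little: that section does not describe the stroke-scale, cognitive or Barthel assessments either, and nobody would conclude that those are made in one arm only. The flow chart, where a screening step would appear, is not available to this review. The exclusion item speaks of operating a smartphone and the training of accessing the intervention, so they may be different steps. Followed strictly, the Analysis section already keeps failers in.

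The size is equally open. Severe cognitive and communication problems are excluded separately, and the caregiver is trained too and helps with access. Failure may be rare and only loosely tied to MRS 4–6.

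All of this stands, and it is why the point is conditional. It does not clear the text. The Barthel and stroke-scale criteria do not depend on anything given to one arm; this one refers to training requirements, and the only such requirements stated belong to the intervention arm and use its content. A reader following the article cannot tell whether an allocated participant who fails stays in.

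**Conclusion.** The point holds as a conflict between stated provisions. The exclusion item, the placement of training and the intention-to-treat rule cannot all operate as written, and a literal use of the exclusion would act on one arm after randomisation. That such exclusion is planned is not established.

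The direction of bias, towards the intervention, needs two conditions: failers are removed from one arm, and they are more dependent than average (*q* above 50%). At *q* = 50% there is no bias. The size is unknown. About 0.5 to 10 percentage points is an illustration under assumed failure of 5–20% and assumed dependency of 60–90% among failers, with a 50% base rate and no true effect. If the criterion is applied to everyone before randomisation, or if all allocated participants are followed and analysed, this bias does not arise.

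**What to change.** Reconcile Exclusion criteria, Randomisation, Intervention arm and Analysis with two statements.

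1. Any criterion on operating a smartphone is assessed in every consenting participant before the entry form is sent for randomisation, without exposing future controls to intervention content. A short generic operation test is one way. Dropping the criterion is another.
2. Nobody is excluded after randomisation for failing the training under Intervention arm. Such participants have the 6-week MRS assessed and are analysed in their allocated arm. Training failure can be reported as adherence.

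The change is to wording, and the formal sample size stays at 266. The cost is a few minutes of screening for everyone, or some dilution from retained failures. If failers gain nothing and others gain 20 points, the average effect is 20 × (1 − *f*): 19 points at 5% failing, 18 at 10%, 16 at 20%. With 106 evaluable per arm (133 × 0.8), one-sided 5% power for a superiority comparison of 50% with 30% goes from 91% with no failures to 88%, 85% and 77%. Dilution is thus slight if few fail and material at 20%, which is a reason to screen both arms alike beforehand. The Analysis section, as it stands, already accepts this dilution.
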